### Evaluation and follow-up

The evaluation process will be conducted by two physiotherapists with experience in the evaluation procedures and blinded to the allocation of the participants to the different groups. Evaluations will be conducted in the following manner:Pre-treatment evaluationEvaluation immediately following a single intervention sessionPost-treatment evaluationEvaluation 1 month after the end of treatmentEvaluation 3 months after the end of treatment

Evaluations will be conducted on three non-consecutive days with a maximum period of 1.5 hours per day.

### Three-dimensional analysis of upper-arm movement kinematics

Upper-arm movement kinematics will be evaluated using the SMART-D 140® system (BTS Engineering, Milan, Italy), which involves eight cameras sensitive to infrared light with a sampling frequency of 100 Hz and a synchronized video system. Passive markers will be positioned on anatomic reference points following the SMARTup protocol (Fig. 2). The markers will be attached directly to the skin using a specific adhesive tape [32, 33]. A total of 18 markers (diameter: 15 mm) will be used to identify the position of the head, trunk, and upper limb (upper arm, forearm, and hand).

**Fig. 2 Fig2:**
[figure not shown]
Placement of markers for three-dimensional analysis (SMARTup protocol). Schematic diagram of frontal and rear views of marker set used for 3D kinematic analysis adapted by Menegoni, 2009 [34]

The positioning of the upper limb will be reconstructed using markers. Twelve markers will be positioned bilaterally in the upper limbs: acromion, lateral epicondyle of the humerus, styloid process of the ulna and radius, head of the second metacarpus and nail of the index finger. The head position will be reconstructed using four markers: two symmetrically in the frontal bone near the timeline and two symmetrically at the back of the head. The trunk position will be estimated using markers positioned on the C7 spinous process and in the jugular notch. An additional marker will be positioned on the target of the movement trajectory.

Based on data published by Menegoni [34], the movement sequence will be in three phases: going phase (i.e., phase toward the target); adjusting phase (i.e., phase dedicated to precisely locating the target); and returning phase (i.e., phase toward initial position) (Fig. 3). At least six reach movement sequences will be performed to obtain three adequate cycles for data processing. The biomechanical model, data filtering and processing of the variables will be performed using the *SMART Analyser* software program (BTS Engineering, Milan, Italy). To evaluate changes after the intervention, the following variables will be identified in each session and the mean of the results will be calculated [32, 33, 35].

**Fig. 3 Fig3:**
[figure not shown]
Sequential phases. Schematic representation of the distance profile between finger and target, during pointing movement. Using a threshold on the distance profile, the adjusting phase was defined Menegoni, 2009 [34]

#### Total movement duration

This is calculated as the total time required for completing each task. The duration of the three phases (going, adjusting, and returning) will also be computed.

#### Mean movement velocity in the going phase

This is the mean velocity of the marker positioned on the index finger.

#### Adjusting sway index

This is the length of the path described by the fingernail in the adjusting phase; it is a measure of the adjustments made to reach the final position and represents the degree of precision.

#### Index of curvature

This is the ratio of the length of the fingernail path to the linear distance between the initial and the final pointing position; representative of movement smoothness during the going phase.

#### Average jerk

This is the mean value of the acceleration derivative (jerk) according to the equation:$$ \mathrm{Average}\ \mathrm{jerk}=\frac{1}{T}{{\displaystyle {\int}_0^T\left[{\left(\frac{{\operatorname{d}}^3x}{\operatorname{d}{t}^3}\right)}^2+{\left(\frac{{\operatorname{d}}^3y}{\operatorname{d}{t}^3}\right)}^2+{\left(\frac{{\operatorname{d}}^3Z}{\operatorname{d}{t}^3}\right)}^2\right]}}^{1/2}\operatorname{d}t $$

in which *x*(*t*), *y*(*t*) and *z*(*t*) are the *x*, *y* and *z* coordinates of the fingernail and *T* is the movement duration. It has been shown that the average jerk index decreases with the increase in the smoothness of movement. This index is often used as a measure of the quality of selective motor control [36, 37].

#### Range of motion of the elbow and shoulder

This is calculated as the difference between the maximum and minimum values of the angle between the frontal plane (shoulder) and sagittal plane (elbow and shoulder) during the going phase [32, 33, 35]

### Electromyographic analysis

Electromyography is the most widely used assessment tool for the study of muscle activation during exercise and the intensity of contractions [38]. The electrical activity of the biceps brachii and triceps brachii muscles will be collected using the eight-camera FREEEMG® electromyography system (BTS Engineering), with a bioelectric signal amplifier, wireless transmission, and bipolar electrodes with a total gain of 2000 and a sampling frequency in the 20–450 Hz range. Impedance and the common rejection mode ratio of the equipment are >10^15^ Ω//0.2 pF and 60/10 Hz 92 dB, respectively. The motor point of the muscles will be identified and the skin will be cleaned with 70 % ethanol to minimize bioimpedance, following the recommendations of SENIAM 8 [39]. Electromyography data will be collected and digitized at 1000 frames per second using the BTS MYOLAB® software program. Electromyography data will be collected concomitantly to the collection of the kinematic data and both sets of data will be managed using the BTS® system and SMART Capture® software program.

### Quality of Upper Extremity Skills Test

This test will be used for the evaluation of manual function. It was developed to evaluate the movement patterns of normal development, which are the basis for the determination of functional upper limb performance. Evaluation of upper limb skills is divided into four areas: dissociated movements (19 items), grasp (6 items), weight bearing (5 items), and protective extension (3 items) [40]. Participants will wear a short-sleeve shirt and will not use any type of brace or adaptation during the evaluation. The rater will either demonstrate the movements or stimulate the participant orally or through the use of toys, but the participant will perform the activities without physical assistance and will maintain the position required for at least 2 s. The QUEST 40 manual furnishes specific information for each dimension and its respective scoring.

### Evaluation of upper limb spasticity

The Modified Ashworth Scale [41] will be used to evaluate spasticity. This scale quantifies resistance during the passive movement of a limb along a given range of motion and furnishes a score ranging from 0 (no increase in muscle tone) to 4 (stiffness).

Elbow extension and flexion will be analyzed. The scale will be administered by physiotherapists blinded to the allocation of the participants to the different groups. The Biomedical Technology Laboratory of the Polytechnic University of Milan has developed a portable device to measure the angle: momentum ratio to allow a high degree of precision in the evaluation of hypertonia. This device consists of two inclinometers and a strain gauge momentum sensor [42], which respectively measure the angle and momentum during elbow flexion and extension, allowing the non-invasive estimation of the passive elastic properties of the elbow. These properties are determined through the measure of the momentum of elbow flexion and extension in relation to the angle of joint motion. The momentum: angle measure will be performed throughout the entire range of motion of the elbow on the sagittal plane. Prior to the measure, the examiner will explain the procedures and how the device functions to the participants and guardians. The estimated execution time for this evaluation is approximately 15 min. The data will be stored and processed to obtain elbow angles during the movement.

### Intervention

#### Transcranial direct current stimulation

Transcranial direct current stimulation will be administered using a DC-STIMULATOR (NeuroConn, Germany) with two sponge (non-metallic) electrodes measuring 25 × 25 cm^2^ moistened in saline solution. The participants will be randomly allocated to active or sham transcranial direct current stimulation over the primary motor cortex following the procedures described by Fregni et al. [17]. The anodal electrode will be positioned over C3/C4 (international 10-20 system of electrode placement), corresponding to the primary motor cortex. The cathode will be positioned in the supraorbital region contralateral to the anode. The anode will be positioned over the primary motor cortex of the contralateral hemisphere to motor impairment. A current of 1 mA [43] will be administered for 20 min in each session. The device has a knob that allows the operator to control the intensity. Stimulation will be gradually increased to 1 mA in the first 10 s and will be gradually diminished in the last 10 s of the session. For sham stimulation, the electrodes will be placed in the same positions and the stimulator will be switched on for 30 s to give the participants the initial sensation, but no stimulation will be administered during the rest of the session. This is a valid control procedure in studies involving transcranial direct current stimulation.

### Immediate effect of transcranial direct current stimulation

Cross-sectional analysis will be conducted to determine the immediate effects of transcranial direct current stimulation. For this, the participants will be submitted to a single 20 min session of transcranial direct current stimulation over the primary cortex while at rest one month prior to the onset of the main intervention. The participants will first be instructed regarding the procedure and will remain at rest for 20 min with the electrodes in place (as described in the previous item). The evaluations will involve QUEST, three-dimensional movement analysis, surface electromyography of the biceps and triceps brachii muscles and the measurement of spasticity of the paretic upper limb. A first evaluation will be made after 20 min of rest and a second evaluation will be made after 20 min of transcranial direct current stimulation (active or sham). The raters will be blinded to the allocation of the participants to the different groups.

### Protocol for functional training of paretic upper limb

The therapy will be based on manual reach with the induced constraint of the non-paretic limb during the transcranial direct current stimulation session following the protocol described by Hoare et al. [6]. In each 20 min session, the participant will be seated in a chair at a height that allows 90° flexion of the hips and knees with the feet supported on the floor. A table with an adjustable height will be positioned in front of the participant. The participant will be positioned to allow free movement of the paretic upper limb for reaching and grasping and allow the visual tracking of the movement. The physiotherapist will be positioned in front of the participant to direct the movement, offering verbal encouragement and any necessary physical assistance to complete the task. Prior to the session, a variety of educational toys and objects, carefully selected for use in the task, will be placed in the therapy room (Fig. 4). To enhance their motivation and attention, participants will be asked to select the toy or object to be used during the task. The three motor strategies that will be trained are grasping, moving objects, and manual range activities. To ensure the intensive use of the paretic upper limb during the session, the non-paretic upper limb will be constrained with the use of a comfortable neoprene glove that does not allow palm grip.

**Fig. 4 Fig4:**
[figure not shown]
Educational toys

After the transcranial direct current stimulation intervention protocol and until the final evaluation (three-month follow-up), the patients will receive physical therapy in two 1 hour sessions per week, directed at the functional activities of gait as well as passive stretching of the trunk, elbow, and wrist of the paretic upper limb to maintain the ranges of motion. No training or unilateral or bilateral stimulation of the upper limbs will be performed, to avoid any conflicts in the expected results of the study.

### Statistical analysis

Statistical analysis will be performed using intention-to-treat analysis. If data losses occur during the study, ‘last observation carried forward’ analysis will be employed to adjust the missing data in the follow-up evaluations. The data will be expressed as mean and standard deviation values. The two intervention groups will be analyzed for differences in anthropometric characteristics as well as clinical and functional variables using the chi-square test for categorical variables and the *t* test for continuous variables. Analysis of covariance (ANCOVA) will be employed to evaluate the effects of transcranial direct current stimulation on the outcome variables of upper limb function. For all analyses, the fixed independent variables will be group (active and sham transcranial direct current stimulation) and evaluation (before the intervention, after the intervention, at 1 month follow-up, and at 3 month follow-up). The dependent variables at baseline will be considered covariables: QUEST, outcomes obtained from three-dimensional movement analysis, electromyography, and spasticity. The ANCOVA will be used to compare effects after the interventions (active versus sham transcranial direct current stimulation), adjusting individual performance prior to transcranial direct current stimulation. This model was considered to be an advantageous approach for statistical analysis considering the nature of the study (randomized with a relatively small sample). Cohen’s *d* (effect size) will be calculated based on the difference in values between baseline and the post-intervention evaluation, with the comparison of the groups. Statistical significance will be considered for *P* < 0.05. Data will be organized and tabulated using the Statistical Package for the Social Sciences (SPSS, v.19.0).

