In the rehabilitation process, the aim of neuromodulation techniques is to increase local synaptic efficacy, thereby altering the maladaptive plasticity pattern that emerges following a cortex lesion. The possibility of combining physical therapy modalities is one of the advantages of transcranial direct current stimulation. Stimulation is a way to modulate cortex activity by opening a path to enhance and prolong functional gains achieved through physical therapy. Stimulation allows a change in a dysfunctional excitability pattern through the activation of specific neural networks so that physical therapy can mold a functional cortex activity pattern [17]. Studies involving the use of transcranial direct current stimulation over the primary motor cortex in stroke victims have demonstrated improvements in upper limb function (active wrist and finger movements), movement velocity, active ankle movements, and overall motor function. However, only a very small number of studies have analyzed the effects of transcranial stimulation in children with cerebral palsy. The literature reports the use of transcranial magnetic stimulation as a way to analyze evoked potentials [23, 24] and as a resource to reduce spasticity in children with cerebral palsy [25, 26].

Analyzing the effects of transcranial magnetic stimulation, a recent study [27] reports significant changes in motor cortex maps in children with hemiparesis or diparesis stemming from cerebral palsy, such as lateral movements of the affected upper limb and motor representation of the affected lower limb, demonstrating reorganization following lesions in one or both hemispheres of the brain. Another recent study [28] employed transcranial direct current stimulation combined with treadmill training in a child with cerebral palsy and found beneficial effects with regard to the acquisition of motor skills. Another study [29], involving children with congenital hemiparesis, concluded that transcranial direct current stimulation appears to be safe, feasible, and well tolerated in most children with hemiparesis, but the authors of that study suggest further investigations of serial sessions of transcranial direct current stimulation in conjunction with rehabilitation for a synergistic approach to improving hand function.

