### Sample size

The sample size was calculated using the STATA 11 program, using a study conducted by Choudhary et al. [31] as the basis. Scores on the Quality of Upper Extremity Skills Test (QUEST) were used for the calculation. Based on the mean and standard deviation values of the experimental group prior to intervention (mean: 76.4; standard deviation: 9.2) and after the intervention (mean: 87.2; standard deviation: 9.4), a bidirectional alpha of 0.05 and 80 % test power, a minimum of 13 children were deemed necessary for each group. The sample will be increased by 20 % to compensate for possible dropouts, leading to 17 children in each group (overall sample: 34 participants).

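### LOCF for missing follow-up scores can bias the 1- and 3-month group comparisons in either direction and leaves out the uncertainty about those scores

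*Protocol article*

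**What the plan says.** The Statistical analysis section sets the principle, "Statistical analysis will be performed using intention-to-treat analysis", and then the rule for missing data: "last observation carried forward’ analysis will be employed to adjust the missing data in the follow-up evaluations". The outcome model is an ANCOVA with the baseline value as covariate and with group and visit as fixed factors. The visit factor is "evaluation (before the intervention, after the intervention, at 1 month follow-up, and at 3 month follow-up", so both off-treatment visits are part of the planned model.

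Training runs for two weeks (Abstract). Evaluations follow at the end of treatment and 1 and 3 months later (Evaluation and follow-up). For the period up to the 3-month visit, the section on functional training of the paretic upper limb says: "No training or unilateral or bilateral stimulation of the upper limbs will be performed". The background section on transcranial direct current stimulation describes stimulation as a way to "enhance and prolong functional gains achieved through physical therapy".

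The Sample size section raises 13 children per group by 20% "to compensate for possible dropouts", giving 17 per group and 34 in all.

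**The concern.** LOCF assumes that a child's score does not move after the last visit attended. That is a strong assumption once the treatment has stopped. The 1- and 3-month visits are off treatment, so what they can add is whether a gain lasts, grows or fades. For a child last seen at the post-treatment visit, LOCF answers that question by assumption: the later change is set to zero. A child last seen before that visit contributes a score from before the training course, in which no training effect can show. A child seen at 1 month but not at 3 months carries the 1-month score.

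At stake are the two follow-up comparisons between active and sham stimulation. Their bias depends on how many children are lost, when, from which arm, and how the group difference develops. In every case the filled-in scores count as real ones, so the uncertainty about them is understated. In a trial of 34 children a few such scores matter.

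**Working it through.** **1. The plan's own figures.** Inputs from Sample size: before intervention "mean: 76.4; standard deviation: 9.2"; after intervention mean 87.2, standard deviation 9.4; "a bidirectional alpha of 0.05 and 80 % test power".

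- Difference: 87.2 − 76.4 = 10.8. Pooled SD: √((9.2² + 9.4²)/2) = 9.30.
- Normal approximation: n = 2 × (9.30 × (1.960 + 0.842)/10.8)² = 11.64, so 12 per group. The exact t-based calculation gives power 0.776 at 12 and 0.811 at 13, so 13 per group, as stated.
- Allowance for loss: 13/(1 − 0.20) = 16.25, so 17 per group, as stated. After rounding, the room is 4/17 = 24% per arm.

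The 10.8 is a before-after change within the experimental group of a cited study, not an active-minus-sham difference. Both arms here receive the same training, so the group difference may be well below 10.8. I use 10.8 as an upper illustration and half of it, 5.4, as a second value.

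**2. Loss after the post-treatment visit.** Let m be the share of each arm last seen at post-treatment, D the group difference at that visit and D3 the true difference at 3 months. With loss unrelated to the scores, the expected LOCF difference at 3 months is

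(1 − m) × D3 + m × D.

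| m | D | D3 = 0 | D3 = D/2 |
|---|---|---|---|
| 10% | 5.4 | 0.54 | 2.97 (true 2.7) |
| 20% | 5.4 | 1.08 | 3.24 (true 2.7) |
| 30% | 5.4 | 1.62 | 3.51 (true 2.7) |
| 10% | 10.8 | 1.08 | 5.94 (true 5.4) |
| 20% | 10.8 | 2.16 | 6.48 (true 5.4) |
| 30% | 10.8 | 3.24 | 7.02 (true 5.4) |

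At m = 20%, LOCF shows 20% of the post-treatment difference when none remains, and 0.8 × 50% + 0.2 × 100% = 60% when half remains. If D3 = D, the formula returns D and there is no bias in the mean.

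**3. Loss before the post-treatment visit.** A score from before training carries an expected group difference of about zero.

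- All 20% lost early and the effect fully lasting: 0.8 × D, so 80% of the true difference is shown.
- Half of the 20% lost early, D = 10.8, effect gone: 0.1 × 10.8 = 1.08 instead of 2.16.
- The same mix with half the effect remaining: 0.8 × 5.4 + 0.1 × 10.8 = 5.4, which equals the truth. The two biases cancel.

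**4. Unequal loss.** Assume that the active arm gains 10.8, the sham arm gains 5.4 and both gains fade fully, so the true difference is 0. All loss is after post-treatment.

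- 30% lost in active, 10% in sham: 0.3 × 10.8 − 0.1 × 5.4 = +2.70.
- 10% in active, 30% in sham: 0.1 × 10.8 − 0.3 × 5.4 = −0.54.

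**5. False-positive rate.** A simulation used 17 per arm, SD 9.3, baseline-adjusted ANCOVA at 3 months, random loss straight after the post-treatment visit, a true 3-month difference of 0, an assumed correlation between visits of 0.7 and 4000 runs per setting. It tests the 3-month visit alone, a simpler model than the planned one.

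| Loss | LOCF, D = 5.4 | LOCF, D = 10.8 |
|---|---|---|
| 10% | 6.0% | 7.2% |
| 20% | 6.1% | 14.0% |
| 30% | 9.5% | 22.4% |

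With correlations of 0.5 and 0.85, the rate for 20% loss and D = 10.8 is 11.8% and 17.0%. Using only observed 3-month scores, the rate was 4.6% to 5.4% in all settings.

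**The case against.** Several points on the other side stand.

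- A reader might infer that LOCF always builds in a lasting effect. It does not: it carries the last observed score, whichever that is, and steps 3 and 4 show dilution, cancellation and a change of sign.
- A reader might take 2.2 QUEST points as the expected bias. The documents give no active-minus-sham difference, no rate of fading and no timing of loss. At D = 5.4 and 20% loss the false-positive rate is about 6%, close to nominal, even with full fading and all loss at the worst moment.
- The 20% is an allowance for possible loss, not a forecast. Even if it were used up, about four fifths of the scores would be observed, so it would be wrong to say that the follow-up results rest on attrition rather than data.
- The primary objective is manual ability before and after training. The sample size rests on a before-after contrast, and Cohen's d on the change from baseline to the post-intervention evaluation. Loss after the post-treatment visit affects neither the comparison at that visit nor Cohen's d. No hypothesis about durability is stated; that purpose is inferred from the off-treatment visits and the background.
- The rule is worded for follow-up evaluations, so it is unclear whether it would also fill a missing post-treatment score. An evaluation after a single session is also listed, so the score carried for an early loss need not be the pre-treatment one.

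A statistical analysis plan, not shown here, may add sensitivity analyses, and their absence from the article is no fault. That does not settle the point, because the article itself chooses LOCF as the method.

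**Conclusion.** The point holds for the 1- and 3-month group comparisons. LOCF as fixed in the protocol can bias them in either direction and understates the uncertainty about the missing scores. With 20% of each arm lost after the post-treatment visit and a group difference that disappears, the spurious 3-month difference is about 1.1 QUEST points (assumed D = 5.4) to about 2.2 (D = 10.8, upper illustration). Over 10% to 30% loss the range is 0.5 to 3.2 points. If the difference does not fade, loss after that visit leaves the mean unbiased.

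The mechanism follows from the text and is certain. The size is not, because the amount and timing of loss, the fading and the group difference are all assumed. The documents do not support extending this to the post-treatment result, nor calling the bias one-directional. The plan should be changed, but the harm is confined to the follow-up comparisons.

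**What to change.** Replace LOCF, and the ANCOVA on LOCF-filled data, with a likelihood-based mixed model for repeated measures. It should use all observed post-baseline scores (post-treatment, 1 month, 3 months), with group, visit, group-by-visit interaction and baseline score as terms. It needs no imputation and is valid if data are missing at random. Keep LOCF, or a return-to-baseline or delta-adjusted imputation, only as a sensitivity analysis for the two follow-up visits, and report the number lost by arm and visit.

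The cost is more than a change of wording: the stated model changes, and intervals at follow-up will be slightly wider because missing scores no longer count as data. A child with no post-baseline score adds nothing to this model and should be reported as such. No new data or visits are needed. Trial status gives recruitment as open at submission; the change should be made and dated before unblinding.

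### The ANCOVA as written has no within-child term and uses baseline as both response level and covariate; fitted that way, it does not hold its nominal 5%

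*Protocol article*

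**What the plan says.** The Statistical analysis section of the protocol article names ANCOVA as the method for the upper limb outcomes and then sets out the model. "For all analyses, the fixed independent variables will be group (active and sham transcranial direct current stimulation) and evaluation". The levels of evaluation are listed as "before the intervention, after the intervention, at 1 month follow-up, and at 3 month follow-up". On covariates: "The dependent variables at baseline will be considered covariables". The purpose is given as "The ANCOVA will be used to compare effects after the interventions (active versus sham transcranial direct current stimulation), adjusting individual performance prior" to stimulation. For losses during follow-up, "last observation carried forward’ analysis will be employed to adjust the missing data in the follow-up evaluations". "Statistical significance will be considered for" P < 0.05, which matches "a bidirectional alpha of 0.05" in the Sample size section.

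The Evaluation and follow-up section confirms that the same children are seen at each of these visits. The article names no child effect, repeated factor, random effect or covariance structure. It also does not say which test from the two-factor model answers the main question: the group effect averaged over visits, group by evaluation, or the contrast at one visit.

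**The concern.** There are two faults in the stated model.

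1. **No within-child term.** Group is a between-child factor, so its error has to come from variation among the 34 children. With only group, evaluation and baseline in the model, the error comes from all rows: 34 × 3 = 102 with post-treatment rows only, or 34 × 4 = 136 with every listed level. The visit-averaged group effect then gets too small a standard error. Group by evaluation, which is a within-child comparison, gets too large a one. Carrying the last observation forward adds rows that copy an earlier score and still count as new information.

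2. **Baseline on both sides.** On the pre-intervention rows the response is its own covariate. Those rows have artificially small residuals and pull the pooled error down. They also dilute the visit-averaged effect: if the true effect is d at each of the three later visits, the average over four levels is (0 + d + d + d)/4 = 0.75d.

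At stake is whether P < 0.05 means what the plan says it means for the active-sham comparison.

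**Working it through.** **Plan's own figure.** The Sample size section gives a pre-intervention QUEST "mean: 76.4; standard deviation: 9.2", and 87.2 (SD 9.4) afterwards. The difference is 10.8 and the pooled SD is √((9.2² + 9.4²)/2) = 9.30. The normal formula 2 × (9.30 × (1.960 + 0.842)/10.8)² gives 11.64, so 12. With the t distribution, power is 77.6% at 12 and 81.1% at 13, so 13 per group reproduces. Then 13/0.8 = 16.25, rounded up to 17. The check below uses 17 per arm.

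**Assumption.** The article gives no correlation between visits. I write ρ for a common correlation between any two visits (compound symmetry) and take 0.3 to 0.9. After adjustment for baseline, the correlation left between post-treatment scores is r = ρ/(1 + ρ).

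**Group main effect, three post-treatment rows.** The true variance exceeds the model's by the factor 1 + 2r, so the actual error is about 2 × (1 − Φ(1.96/√(1 + 2r))). Simulation under no effect (4,000 runs; ordinary ANCOVA with group, evaluation, their interaction and baseline) agrees:

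| ρ | r | 1 + 2r | formula | 3 rows | 4 rows | one record per child |
|---|---|---|---|---|---|---|
| 0.3 | 0.231 | 1.46 | 10.5% | 10.3% | 8.4% | 5.0% |
| 0.5 | 0.333 | 1.67 | 12.9% | 12.8% | 11.4% | 4.7% |
| 0.7 | 0.412 | 1.82 | 14.7% | 15.0% | 14.1% | 4.9% |
| 0.8 | 0.444 | 1.89 | 15.4% | 15.5% | 15.0% | 5.0% |
| 0.9 | 0.474 | 1.95 | 16.0% | 15.9% | 15.8% | 4.7% |

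**Post-treatment scores more alike than baseline.** If baseline correlates b with each later visit and later visits correlate p with each other, r = (p − b²)/(1 − b²). With b = 0.7 and p = 0.9, r = (0.9 − 0.49)/0.51 = 0.80. Simulation with r set at 0.8 gives 22.4% (three rows) and 21.3% (four rows). A separate simulation with post-visit correlation up to 0.9 and baseline correlation 0.5 to 0.7 tops out at 22.6% and 21.7%. At the extreme r = 0.95 the three-row figure is 25.3%. One record per child stays between 4.4% and 5.2% across the runs with r set directly.

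**Group by evaluation, three rows.** The within-child error is only (1 − r) of the pooled error. In large samples the actual level is 0.05^(1/(1 − r)) = 0.05^(1 + ρ): 2.0% at ρ = 0.3 and 0.3% at ρ = 0.9. Simulation gives 0.4 to 1.9% with three rows and 1.2 to 4.1% with four.

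**Active-sham contrast at post-treatment.** With three rows, simulation gives 4.5 to 5.8%, close to nominal. With baseline rows kept and unit variance, the common slope is (1 + 3ρ)/4. The residual variance is V0 = (3(1 − ρ)/4)² on baseline rows and V1 = 1 − ρ² + ((1 − ρ)/4)² on later rows. The model uses (V0 + 3V1)/4 where V1 is needed.
- ρ = 0.3: V0 = 0.276, V1 = 0.941, pooled 0.774. SE ratio √(0.774/0.941) = 0.907; 1.96 × 0.907 = 1.78; error 7.5%.
- ρ = 0.9: V0 = 0.006, V1 = 0.191, pooled 0.144. SE ratio 0.870; 1.96 × 0.870 = 1.71; error 8.8%.

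These are normal approximations. Simulation gave 7.5 to 8.6% in one set of runs and about 8 to 10% in another.

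**The case against.** The strongest reply is that independence of rows is read into silence. Group and evaluation are also the fixed factors in a mixed model with a random child effect, and in a repeated-measures ANCOVA with evaluation as the within-subject factor. The article is condensed, and a covariance structure is the sort of detail left to a fuller plan. The Study design section calls the trial paired, and the analysis text speaks of adjusting for individual performance. A reader might infer that the sponsor will pool 102 to 136 rows as independent and that the trial's false-positive rate is therefore far above 5% throughout. The documents do not support that: they neither state such a fit nor exclude a repeated-measures one.

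The reply is also right that the inflation is not general. It falls mainly on the visit-averaged group effect, which the plan never names as its test. With baseline rows out, the post-treatment contrast is near nominal even in the pooled fit, and group by evaluation errs in the conservative direction.

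Two things remain. The article does give a model for all analyses, with factors, levels and covariates, and that model as stated is not valid for its group test. Using baseline both as a response level and as a covariate is explicit in the text. No unseen detail about covariance would mend it, and a repeated-measures fit would still carry the 0.75 dilution.

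**Conclusion.** The point holds for the model as written. With 17 per arm and a nominal two-sided 5%, the group main effect rejects about 8 to 16% under compound symmetry with ρ from 0.3 to 0.9. It rejects up to about 23% if post-treatment scores correlate more with each other than with baseline. The post-treatment contrast rejects about 8 to 10% when baseline rows are kept, and group by evaluation about 0 to 4%. A one-record-per-child ANCOVA holds about 5%. The sizes rest on assumed correlations, complete data and an ordinary ANCOVA fit; the added effect of carried-forward rows was not quantified. Whether the sponsor would fit it that way cannot be settled from the article, but the text should be corrected before analysis because it governs the trial's main comparison.

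**What to change.** Rewrite the model description:

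- Take the pre-intervention visit out of the levels of evaluation, and keep each outcome's own baseline as covariate.
- Analyse the post-treatment, 1-month and 3-month scores with a model that accounts for repeated measures within child. An example is a mixed model with group, evaluation, group × evaluation, baseline and a stated within-child covariance. Alternatively, run a one-row-per-child ANCOVA at each visit.
- Name the active-sham contrast at post-treatment as the main test. This fits the article's own effect size, which is based on the change from baseline to the post-intervention evaluation.

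The cost is wording and a different standard procedure, with no new data. The interval for the visit-averaged group effect becomes wider than the pooled fit would show, by √(1 + 2r): √1.46 = 1.21 to √1.95 = 1.40 times over the compound-symmetry range. That is the width it should have.
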